## Introduction

### Background

Physical activity (PA) is widely recognized as a cornerstone of public health due to its proven effectiveness in preventing and managing noncommunicable diseases [1]. However, PA has emerged as an escalating global health and socioeconomic challenge [2], significantly impacting the Spanish population, particularly in the autonomous Community of Madrid (CAM), where more than 39% of the adults fail to meet World Health Organization (WHO) guidelines [3]. In occupational contexts, this is especially concerning due to the negative association between inactivity and work ability, a key predictor of productivity, employment sustainability, and healthy aging in the workforce [4,5].

PA can be classified into different domains, with leisure-time physical activity (LTPA) and occupational physical activity (OPA) being particularly relevant in work-related health research [6,7]. OPA refers to the physical effort involved in work-related tasks [8], whereas LTPA encompasses voluntary activities, such as exercise, sports, and recreation [6]. Although both contribute to total PA, their effects on health are not equivalent [4,6-9].

Substantial evidence links high levels of LTPA with enhanced overall health, lower risk of noncommunicable diseases, and improved mental and musculoskeletal health [1,9]. Conversely, high OPA levels have been associated with increased risks of musculoskeletal disorders (MSDs) [10], cardiovascular diseases [10,11], and higher mortality rates. This apparent contradiction, referred to as the “PA paradox,” highlights that OPA often lacks sufficient intensity, involves prolonged durations without recovery, and typically occurs under low-autonomy conditions [11]. This paradox provides a relevant conceptual framework for this study, reinforcing the importance of examining LTPA and OPA as distinct domains with potentially divergent effects on work ability.

Moreover, while LTPA has been shown to positively influence occupational outcomes, including work ability [12], reduced absenteeism [13,14], greater job satisfaction [15], improved performance, and higher productivity [16,17], an imbalance between OPA and LTPA may lead to diminished functional capacity, increased absenteeism, and an elevated risk of burnout [11-13,17-21].

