Although international guidelines, such as those issued by the WHO, define minimum PA thresholds for various age groups and conditions [20], social determinants of health, including gender, sex, socioeconomic status, and workplace environment, play a significant role in shaping individuals’ ability to meet these recommendations [22-29]. In this context, unequal access to LTPA opportunities contributes to the persistence of health disparities [20,21].

Gender and sex play a particularly important role in shaping PA behavior and work-related outcomes. Women tend to engage in less LTPA than men, a pattern observed in Spain and the CAM region, where 46.89% of the women report being sedentary compared to 30.61% of the men [3]. This disparity is likely driven by a combination of gender- and sex-related factors. Gender-based determinants may include unequal caregiving responsibilities, reduced time for leisure due to social roles, and cultural expectations regarding self-care and productivity, which can limit women’s participation in LTPA [22,23,30]. In contrast, sex-related factors, such as menopause, endometriosis, and urinary incontinence (biological or physiological processes specific to female reproductive health), may directly impact physical capacity and perceived work ability [24]. These distinct but intersecting influences are often overlooked in occupational health research, highlighting the need for a gender-sensitive and sex-aware approach.

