### Objectives

On the basis of the aforementioned background, the primary objective of this study is to analyze the relationship between LTPA and work ability among university staff in the CAM, considering the potential modifying effect of OPA, and exploring differences by sex and gender. The secondary objectives are to (1) determine the prevalence of MSDs in this population and analyze their association with LTPA and OPA levels using validated questionnaires; (2) evaluate the relationship between both domains of PA and perceived physical and mental workload, adjusting for occupational role and sociodemographic factors; (3) examine the association between LTPA and OPA and self-perceived health-related quality of life (HRQoL); and (4) explore whether these associations vary according to sex, gender, and occupational category.

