#### Primary Variables

The primary variables include LTPA, OPA, and work ability. LTPA and OPA are assessed using the Spanish version of the Global Physical Activity Questionnaire [41]. This tool assesses PA in 3 domains: occupational, active transport, and leisure, yielding weekly metabolic equivalent of task (MET) minutes for each. MET minutes are calculated by multiplying activity duration by the standard MET values.

The official Spanish version of the questionnaire, endorsed by the WHO, has shown good test-retest reliability (intraclass correlation coefficient=0.70-0.90) and moderate concurrent validity (Spearman ρ≈0.42) compared with the accelerometry in European and Latin American Spanish-speaking populations. Although it has not been formally validated in Spain, its widespread international use and standardization support its inclusion in this study [42].

Work ability is being assessed with the Spanish version of the Work Ability Index (WAI) [43]. The WAI measures 7 dimensions: current work ability compared to lifetime best, work ability in relation to job demands, physician-diagnosed illnesses, estimated work impairment due to illness, sick leave over the past year, prognosis of work ability over the next 2 years, and mental resources. Total scores classify work ability into 4 categories: poor (7-27), moderate (28-36), good (37-43), and excellent (43,45-49). The WAI has been adapted and endorsed by the Spanish National Institute for Safety and Health at Work (NTP 1147) for the Spanish occupational context [43]. It was validated in a sample of 1184 Spanish health center workers, demonstrating satisfactory reliability (intraclass correlation coefficient>0.75), a stable 2-factor structure, and convergent validity with measures of health and productivity, reflecting strong psychometric properties in occupational settings [44].

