### Planned Data Analysis

Descriptive analyses will summarize all variables, reporting means, medians, SDs, and quartiles for continuous variables and frequency distributions for categorical variables. Normality will be assessed using the Kolmogorov-Smirnov test.

To examine associations between PA levels (both OPA and LTPA) and the primary outcomes (work ability, musculoskeletal health, and quality of life), multiple linear and logistic regression model analyses will be performed, depending on the nature of the outcome variable. These models will adjust for relevant covariates, including age, sex, occupational group, and key social determinants of health. Moderation by gender will be assessed through the inclusion of interaction terms, and stratified analyses by sex and gender will be conducted to explore potential differential effects.

To account for the expected heterogeneity across occupational roles, key analyses will be stratified by job category (PDI or PI vs PTGAS). Occupational role will also be included as a covariate in multivariable regression models to adjust for its potential confounding effect. In addition, subgroup analyses will be conducted to explore interaction effects between occupational role and levels of OPA and LTPA on primary and secondary outcomes, including work ability, MSDs, perceived workload, and HRQoL. PA levels will be categorized using WHO-recommended cutoffs, with high PA defined as 600 MET-minutes per week or more, allowing for group comparisons (eg, high vs low OPA or LTPA) in relation to health and occupational outcomes.

Furthermore, mediation analyses will be conducted to evaluate whether MSDs mediate the relationship between PA and work ability. These analyses will follow sequential multiple regression models, applying the approach described by Preacher [51] and Hayes [52] and adapted for cross-sectional data. Model fit will be assessed using the *R*² coefficient and *F* test. Statistical significance will be set at *P*<.05, and 95% CIs will be reported for all regression coefficients.

This analytical approach aligns with a gender-sensitive framework, enabling the detection of differential effects and the potential moderating roles of gender in the relationships between PA, occupational factors, and health outcomes.

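### The 600 MET-min/week cutoff marks a minimum, yet it defines 'high' for both leisure and occupational activity, so low-volume and heavy occupational exposure share one group

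*Protocol article*

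**What the plan says.** In the protocol article, Primary Variables, the Global Physical Activity Questionnaire is described as "yielding weekly metabolic equivalent of task (MET) minutes for each" domain, so LTPA and OPA each arrive as a quantity. On how that quantity is built, the section says only that "MET minutes are calculated by multiplying activity duration by the standard MET values", without listing the values.

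Planned Data Analysis first announces linear and logistic regressions: "To examine associations between PA levels (both OPA and LTPA) and the primary outcomes". It does not state how LTPA and OPA enter those models. Two paragraphs into the regression plan, after the stratified and subgroup analyses by job category, it says that "PA levels will be categorized using WHO-recommended cutoffs", and gives one cutoff: "high PA defined as 600 MET-minutes per week or more, allowing for group comparisons (eg, high vs low OPA or LTPA"). No second cutoff and no separate OPA cutoff appears.

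Three other statements bear on this. Background says that WHO guidelines "define minimum PA thresholds for various age groups and conditions". Background also adopts the physical activity paradox as the framework and says that "OPA often lacks sufficient intensity, involves prolonged durations without recovery". Objectives states the primary aim as the LTPA and work ability relationship, "considering the potential modifying effect of OPA, and exploring differences by sex and gender".

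**The concern.** Two things are wrong with the cutoff as written.

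First, the label. The document treats WHO thresholds as the least a person should do. Reaching a minimum is then called 'high'. For LTPA this is mainly a matter of naming, because whether someone reaches the minimum is a sensible thing to report.

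Second, the transfer to OPA. The study asks whether high occupational load changes how LTPA relates to work ability. The Background ties the harmful form of that load to long duration and lack of recovery. A group intended to represent it should therefore separate substantial occupational effort from a little of it. If the line sits at a small daily volume, the 'high OPA' group mixes the two, and any difference in the LTPA association between heavy and low exposure is averaged down.

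In addition, replacing a measured quantity by two groups loses precision wherever it is done, and the per-domain MET-minutes are already being collected.

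**Working it through.** **The plan's own figure.** The 600 MET-min/week cutoff is stated, not derived, so there is no calculation to reproduce. The sample size (796, or 885 after 10% dropout) does reproduce, but it was set for the precision of a proportion and does not bear on this cutoff.

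**Step 1: what 600 MET-min/week means at work.** The article gives no MET values, so I assume a range of 3 to 8 and a five-day week. Minutes per week = 600 / MET; minutes per working day = that / 5.

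- 3 METs: 600/3 = 200 min/week; 200/5 = 40 min/day.
- 4 METs: 600/4 = 150 min/week; 150/5 = 30 min/day, which is 30/480 = 6.25% of an assumed 8-hour day.
- 8 METs: 600/8 = 75 min/week; 75/5 = 15 min/day.

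'High OPA' therefore starts at about 15 to 40 minutes per working day.

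**Step 2: who shares that group.** Four hours a day at 4 METs gives 4 × 60 × 5 × 4 = 4,800 MET-min/week, and 4,800/600 = 8 times the cutoff. A worker with 30 minutes a day at the same intensity is placed in the same category. The contrast here is one of volume: 'low' means few minutes, not low intensity.

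**Step 3: information lost by one split.** For a normal exposure with a linear effect, the share of information kept after splitting so that a fraction q lies above the cutoff c is φ(c)² / [q(1 − q)], where φ is the standard normal density and c is the matching quantile.

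| Share above cutoff | Kept | Lost |
|---|---|---|
| 50% | 0.64 | 36% |
| 30% or 70% | 0.58 | 42% |
| 20% or 80% | 0.49 | 51% |
| 10% or 90% | 0.34 | 66% |

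The median split is the best case, which is where 'at least about 36%' comes from.

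**Step 4: sensitivity to the distribution.** Activity data probably include many zeros and a long right tail. I simulated 30 to 70% zeros, with lognormal non-zero values (median 800 to 1,500 MET-min, log-SD 0.8 to 1.0; all assumptions). The squared correlation of the ≥600 indicator with log(1+x) was about 0.51 to 0.88. With untransformed MET-minutes it was roughly 0.2 to 0.6. The loss can therefore be smaller or larger than the normal-theory figures, depending on how many staff report zero and on which scale the effect is linear.

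**The case against.** The strongest reply is that the cutoff may not reach the main models. Its stated purpose is group comparisons, and it closes the paragraph on stratified and subgroup analyses. The regression paragraph does not fix the coding of LTPA and OPA, and an article may leave that to an analysis plan that is not shown here. This stands. The regressions refer to PA levels, the same term that is later categorised, but that is suggestive and not proof. The information loss can be asserted only where the split is actually used.

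A reader might go further and infer that the test of LTPA by OPA loses most of its effective sample. The article does not support a figure for that. It writes interaction terms for gender and examines occupational role with OPA and LTPA, but states no LTPA×OPA term. The shares above 600 are unknown, and normality and independence of the two exposures are assumptions.

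A reader might also infer that a null modification result would mean nothing. That is too strong. It would answer a coarser question: whether the LTPA association differs between staff below and above 600 MET-min/week of OPA. Stratification by job category and the physical-demand subscale of the workload index offer other views of occupational load, though neither replaces an OPA measure.

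None of this touches the label or the OPA cutoff, which are stated in the text and not corrected elsewhere.

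**Conclusion.** The point holds for the categorisation as stated. One cutoff, at a level the document itself treats as a minimum, is called 'high' and applied to OPA, where it is reached at about 15 to 40 minutes per working day (assuming 8 down to 3 METs and five days). Low-volume and heavy occupational exposure then fall in one group, and the OPA contrast that the primary objective depends on is blurred. The further loss of information is at least about 36% per split exposure under normality. Its actual size is unknown because the distribution is unknown and probably skewed. Whether it affects the regressions depends on a coding choice the article does not state. This is an inexpensive improvement to make before analysis, not a flaw that invalidates the study.

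**What to change.** In Planned Data Analysis:

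- State that the regression models enter domain-specific LTPA and OPA as continuous MET-min/week, for example log(1+x) with an indicator for zero.
- Examine modification by an LTPA×OPA term on that scale, and name the product terms in advance. There is one if only the log terms are multiplied, and four (2 × 2) if the zero indicators are multiplied as well.
- Keep ≥600 MET-min/week for LTPA only, worded as meeting the WHO minimum.
- Remove the 'high OPA' label at ≥600. Display OPA as none plus tertiles of the non-zero values. Plain quartiles could collapse if many staff report no OPA.

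The data are already collected in the needed form, and the article says no analysis has been conducted, so the change can be made before results are seen. The cost is a few more model terms and coefficients that are harder to read; reporting predicted work ability at chosen MET levels deals with the latter. One limit remains: continuous MET-minutes describe volume and still do not capture recovery or autonomy, which the paradox also involves. The report should say so.

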#### Secondary Variables

Secondary variables include the prevalence of MSDs, HRQoL, and physical and mental workload. MSDs are being evaluated using the Spanish version of the Standardized Nordic Questionnaire [45], which identifies symptoms across various anatomical regions and their functional impact. It includes symptom checklists and related consequences, such as reduced activity or health care visits. This questionnaire has been validated across multiple Spanish occupational samples. In a study of 526 nursing assistants in Asturias, the questionnaire demonstrated good test-retest reliability (Cohen κ=0.60-0.81) and internal consistency (Kuder-Richardson 20=0.74-0.87) [46]. In addition, in a separate validation among 312 professional musicians in Madrid, similar values were observed (Cohen κ=0.60-0.81; Kuder-Richardson 20=0.737-0.873), and construct validity was supported by significantly higher disability and pain scores in anatomical regions with reported symptoms [45]. The tool also demonstrated high feasibility, with an average completion time of 6 (SD 2) minutes [45].

HRQoL is being assessed using the Short Form-12 Health Survey [47], which covers 8 health dimensions across physical and mental domains. Scores are standardized to a population mean of 50 (SD 10); scores greater than 50 indicate better-than-average perceived health. The Short Form-12 Health Survey, validated in a representative Spanish adult population (n≈11,000), reported high internal consistency (Cronbach α=0.87 for the physical component summary and Cronbach α=0.86 for the mental component summary). It accounted for more than 90% of the variance observed in the Short Form-36 Health Survey, further supporting its reliability and construct validity for assessing HRQoL [48].

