Sex and gender are addressed in this study as central determinants of health, given their potential to shape PA behaviors, work ability, and health outcomes in complex and interrelated ways. Globally, women engage in less PA than men [2], a pattern also observed in Spain where inactivity rates range from 22.9% to 40.3% in men and 30.5% to 32.3% in women [2,56,57] and in the CAM region where 46.89% of the women report being sedentary compared to 30.61% of the men [3]. This disparity may reflect traditional caregiving roles, which often limit women’s opportunities for recreation (including LTPA) and self-care [22,23,30] as well as unique physiological and pathophysiological processes related to women’s health [24]. These factors suggest that women may derive fewer benefits from LTPA for work ability under equivalent occupational demands. Furthermore, life stages, such as menopause, are associated with decreased work ability [58,59], highlighting the relevance of exploring these associations in this subgroup.

MSDs, included in this study, are the most common and disabling occupational illnesses [27,60]. They are linked to reduced HRQoL [26], diminished functional capacity [61], and lower work ability [25-27,62]. While high OPA levels may contribute to MSD development [10], appropriate levels of LTPA could serve a protective role [1,63]. However, MSDs may also limit participation in LTPA, potentially creating a feedback loop that further compromises work ability. Similarly, high physical and mental workload is associated with lower LTPA participation [19], higher occupational demands, reduced work ability [64], and increased MSD prevalence, as reported by Saremi et al [65].

Finally, despite numerous workplace PA interventions aimed at improving work ability, many have failed to achieve outcomes beyond physical fitness [4]. This may be partly due to insufficient consideration of occupational demands and individual factors when designing LTPA programs [4]. The findings of this study will provide critical insights into the balance between LTPA and OPA, supporting the design of future interventions with a gender-sensitive approach. Ultimately, this could serve as a valuable tool to prevent noncommunicable diseases and promote optimal work ability among the working population in CAM.

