### Strengths and Limitations

This protocol presents several strengths. First, it uses validated and widely used instruments to assess LTPA, OPA, work ability, and relevant covariates, alongside comprehensive sociodemographic data. The online, self-administered format of the questionnaire reduces potential bias associated with interviewer-led responses and facilitates participation across diverse occupational groups. By collecting key covariates, this study is designed to account for potential confounding factors, ensuring that observed associations are more likely attributable to the primary research objectives. In addition, the estimated sample size provides adequate statistical power to detect significant associations, and the inclusion of participants with varied occupations and occupational demands enhances the generalizability of findings to the broader CAM working population.

The primary limitation of this study is its cross-sectional design, which precludes causal inference between the variables of interest. Longitudinal and interventional studies will be necessary to establish causal relationships and evaluate the effectiveness of tailored PA interventions. In addition, the use of a nonprobability sampling strategy, necessitated by institutional data protection constraints, may introduce selection bias and limit representativeness. However, the multichannel recruitment approach has been carefully designed to promote broad dissemination across occupational groups, and the anticipated heterogeneity of the sample is considered sufficient for the study’s exploratory objectives. Moreover, the use of self-reported measures introduces the possibility of reporting bias, which could affect the accuracy of certain variables. Nevertheless, the use of validated instruments mitigates this concern to some extent. Finally, the absence of objective PA measurements (eg, accelerometers or step counters) may limit the precision of exposure assessment; however, this was a deliberate decision made during the study design phase to prioritize anonymity and feasibility, and it will be addressed in future phases involving subsamples with identifiable data.

As all questionnaire items are mandatory, missing data are not expected. Nonetheless, any unexpected data loss (eg, due to technical issues) will be managed using listwise deletion.

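### The planned mediation test cannot tell whether MSDs lie between LTPA and work ability or whether MSDs limit LTPA, and the WAI may partly score the same MSDs

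*Protocol article*

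**What the plan says.** - **Analysis.** Planned Data Analysis states that "mediation analyses will be conducted to evaluate whether MSDs mediate the relationship between PA and work ability". It uses sequential multiple regressions described as "adapted for cross-sectional data", with significance at P<.05. What is adapted is not said.
- **Direction.** Anticipated Findings gives both directions as possibilities. One is that "appropriate levels of LTPA could serve a protective role" against MSDs. The other is that "MSDs may also limit participation in LTPA, potentially creating a feedback loop that further compromises work ability". For OPA, only the path from OPA to MSDs is mentioned.
- **Outcome.** Primary Variables lists among the seven WAI dimensions "physician-diagnosed illnesses, estimated work impairment due to illness, sick leave over the past year".
- **Mediator.** Secondary Variables says the MSD questionnaire covers symptoms and functional impact, including "symptom checklists and related consequences, such as reduced activity or health care visits".
- **Timing.** Data Collection puts all instruments into one online form.
- **Caveat.** Strengths and Limitations names the "cross-sectional design, which precludes causal inference between the variables of interest". It does not tie this to the mediation analysis and does not mention shared content between the MSD questionnaire and the WAI.

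**The concern.** A mediation test by sequential regression assumes an order: PA first, then MSDs, then work ability. With one measurement, that order is imposed and not observed. The Discussion itself offers the rival structure, in which MSDs reduce both LTPA and work ability. That structure gives the same two non-zero regression paths, so a significant result does not discriminate between the two.

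The overlap adds a second difficulty. If MSDs count among the illnesses that the WAI scores, a person with an MSD loses WAI points partly because of how the score is built.

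The stake is the mechanism that gets reported. The Discussion and Conclusions say the findings should support intervention design and public policy. A statement that LTPA helps work ability by reducing MSDs would point interventions one way; MSDs limiting LTPA would point them another.

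**Working it through.** **The plan's own figure.** The article gives no figure for the mediation analysis, so its sample size is used. With N=3117, z=1.96, p=0.5 and e=0.03 (Sample Size):

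n = N·z²·p(1−p) / [e²(N−1) + z²·p(1−p)] = 795.1, rounded up to 796; 796/0.9 = 884.4, rounded up to 885. Both stated figures reproduce. The check uses n=796.

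**Assumptions (not in the article).** MSD is yes/no with prevalence π = 10-50%. MSD lowers LTPA by d = 0.1, 0.2 or 0.3 SD and lowers WAI by 0.5 SD. LTPA has a direct effect on WAI of 0.15. LTPA has no effect on MSDs, so nothing is mediated. Tests are two-sided at 5%.

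**What the planned regressions estimate here.**
- Path a (MSD on LTPA): a = −d·π(1−π) / [1 + d²·π(1−π)]. This is not zero although LTPA does nothing to MSDs.
- Path b (WAI on LTPA and MSD): b = −0.5.
- Example with d=0.2, π=0.5: a = −0.05/1.01 = −0.0495; a·b = 0.0248; share called mediated = 0.0248/(0.0248+0.15) = 14%.

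**How often this is significant.** The expected z for path b is 0.5·√(n·π(1−π)), which is 7.1 at π=0.5 and 4.2 at π=0.1, so b is nearly always significant. The rate for a·b is therefore close to that for path a, with expected z = d·√(n·π(1−π)):

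| MSD lowers LTPA by | z at π=10% | approx. rate | z at π=50% | approx. rate |
|---|---|---|---|---|
| 0.1 SD | 0.85 | 13% | 1.41 | 29% |
| 0.2 SD | 1.69 | 39% | 2.82 | 81% |
| 0.3 SD | 2.54 | 72% | 4.23 | 99% |

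Simulation with a Monte Carlo 95% CI for a·b gives about 14-30%, 37-80% and 70-99%, which agrees within simulation error. At π=20% the simulated rates are 59% (0.2 SD) and 92% (0.3 SD). At π=50% the median share called mediated is 7%, 14% and 19%.

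**A second parameterisation.** Take MSD as a continuous score, no direct LTPA effect, and an MSD-WAI effect of 0.2-0.5. False mediation then appears in 25-33% of runs at an MSD-LTPA correlation of 0.05, 80-83% at 0.10, 99% at 0.15 and 100% at 0.20.

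**Overlap alone.** With PA and MSDs independent and the MSD-WAI link coming only from scoring, the rate is 4-5% at n=796 however strong the link. Overlap raises b but cannot create a.

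**The case against.** The strongest case on the other side has five parts.

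1. **The article already disclaims causality.** It calls the cross-sectional design its primary limitation, calls its objectives exploratory, and does not list mediation among the objectives. This lowers the weight of the point. It does not remove it: the caveat is general, the adaptation is unnamed, and no regression on one-time data recovers direction.
2. **The error rate depends on assumptions.** This stands. A reader might infer that a mediated effect will appear whenever none exists. The documents do not support that. They say MSDs may limit LTPA, not that they do; the rate is modest at 0.1 SD and nominal when PA and MSDs are unrelated. The reverse path is raised for LTPA only, not for OPA.
3. **Overlap is not false mediation.** This stands. If LTPA truly affects MSDs and MSDs lower the measured WAI, there is a real indirect effect on that measure. Calling it spurious would need a notion of core work ability that the article does not define. The two instruments also differ in content, and the overlap assumes that MSDs are among the illnesses scored.
4. **Model form.** The sentence beginning "Model fit will be assessed using the" names R² and the F test. One might infer that these will be misapplied to a logistic mediator model, or that log-odds and linear coefficients will be multiplied. The article does not fix the coding of MSDs in this analysis and allows linear or logistic models by outcome type, so this is not an established error.
5. **Fitting both orderings cannot decide between them.** This is correct. Both three-variable models are saturated and fit equally well. In simulations of genuine mediation at n=796 (LTPA-MSD log-odds −0.3 per SD, MSD lowering WAI by 0.4-0.5 SD, direct effect 0.15), the reverse ordering was also significant in 97-98% of runs. A rule rejecting mediation whenever both are significant would nearly always reject true mediation.

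**Conclusion.** The point holds in a limited form. The article fixes a significance-tested mediation analysis whose result, for LTPA, cannot distinguish mediation from a reverse path that the article itself raises. Moderate reverse effects (0.2-0.3 SD) would often or nearly always yield a significant indirect effect with no mediation present; small ones (0.1 SD) would do so in roughly one study in seven to one in three. These rates rest on assumed effect sizes and an assumed prevalence of 10-50%. The possible sharing of content with three WAI dimensions affects the size of the MSD-WAI path, not the existence of false mediation.

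A reader might infer that the article contradicts its own statement on causal inference. It does not do so yet: that depends on how the result is worded when reported. The primary LTPA-WAI analysis is not invalidated by this point. The change should be made, and it still can be, since the article reports that no analysis has been run.

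**What to change.** In Planned Data Analysis:

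1. Replace the mediation test with an exploratory analysis of indirect associations, and state that it supports no claim that MSDs mediate the relation.
2. For LTPA, report the reverse ordering (MSD, then LTPA, then WAI) beside the planned one, to show that the data cannot choose between them. Attach no decision rule based on fit or significance.
3. Keep total WAI as the outcome. Add a sensitivity analysis with WAI excluding diagnosed illnesses, impairment due to illness and sick leave, and state there that the MSD questionnaire and the WAI may share content.

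The cost is a few extra model runs on data already being collected. The restricted score has no validation cited in the article and does not map to the WAI categories, so it should remain a sensitivity analysis. The mechanistic claim becomes weaker.
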